**Methods:**

A total of 50 adult patients with DOC due to TBI and 25 healthy subjects will be enrolled in the study. Patients enrolled in the study will be assigned to the EA group or the sham‐EA group through stratified randomization. All patients receive behavioral assessments (CRS‐R and brain–computer interface), neurophysiological evaluations (EEG, somatosensory evoked potentials, brainstem auditory evoked potentials), and neuroimaging evaluations (rs‐fMRI, amide proton transfer, intravoxel incoherent motion, neurite orientation dispersion and density imaging) before and after the 14‐day EA or sham‐EA treatment. Each healthy subject will receive a set of neurophysiological and neuroimaging examinations but no treatments. The practitioner administering EA and sham‐EA is the only one aware of the grouping results. In the sham‐EA group, sham‐acupoints, sham‐acupuncture, and sham‐wire are utilized. The primary outcome measurement is the change in CRS‐R score after 14 days of treatment compared with the baseline CRS‐R score.

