### Study Procedures

2.8

At the time point of screening, demographics, education, time from injury, injury location, right‐ or left‐handed, medical history, current medications, CRS‐R score, and state of DOC are recorded (Table 1). After the enrollment, the following neurophysiological and neuroimaging examinations are performed before the first EA or sham‐EA treatment: EEG, somatosensory evoked potential (SEP), brainstem auditory evoked potential (BEAP), resting‐state functional MRI (rs‐fMRI), amide proton transfer (APT) imaging, intravoxel incoherent motion (IVIM) imaging, neurite orientation dispersion and density imaging (NODDI), and BCI. During the 14 days of treatment, the CRS‐R score is assessed every day after the treatment. After the last EA or sham‐EA treatment, the CRS‐R score and the above‐mentioned neurophysiological and neuroimaging examinations are performed again. During hospitalization, vital signs and adverse events (AEs) are monitored, and concomitant treatments are documented. Glasgow Outcome Scale‐Extended (GOS‐E) score at 30 and 90 days after randomization are collected.

**TABLE 1 brb370637-tbl-0001:** Timing and content of the study assessments.

Items	Day of enrollment					
	Screening	Pre‐treatment assessments	14‐day treatment	Post‐treatment assessments	Follow up	
					30 days	90 days
Written informed consent	●					
Inclusion and exclusion criteria	●					
Demographics	●					
Education	●					
Time from injury	●					
Brain injury location	●					
Right‐ or left‐handed	●					
Medical history	●					
Current medication	●					
Physical examination	●					
CRS‐R score	●		●	●		
State of consciousness	●		●	●		
Brain–computer interface assessment		●		●		
EEG, SEP, BAEP		●		●		
rs‐fMRI, APT, IVIM, NODDI		●		●		
GOS‐E					●	●
Vital signs monitoring	●	●	●	●		
Adverse events			●	●		
Concomitant therapies	●					

Abbreviations: APT, amide proton transfer; BAEP, brainstem auditory evoked potential; CRS‐R, Coma Recovery Scale‐Revised; EEG, electroencephalogram; GOS‐E, Glasgow Outcome Scale‐Extended; IVIM, intravoxel incoherent motion; NODDI, neurite orientation dispersion and density imaging; rs‐fMRI, resting‐state functional MRI; SEP, somatosensory evoked potential.

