### Statistical and Analytical Plan

2.13

Under the Intention To Treat principle, all patients who are randomized are included in the analysis of the original allocation group. Baseline and demographic characteristics such as gender, age, time from injury, brain injury location, closed or open TBI, right‐ or left‐handed, GCS score, CRS‐R score, APACHE2 score, etc., will be pooled by treatment group to assess comparability of treatment groups. The primary outcome of the change in CRS‐R score after 14‐day treatment, secondary outcomes of BCI accuracy after 14‐day treatment and the GOS‐E score at 30 days and 90 days will be analyzed using Student's t‐test or Mann‐Whitney U test (whichever is proper) and will be analyzed by bootstrap analyses in general linear models to estimate adjusted odds ratios and associated 95% confidential intervals (adjusted for age, sex, time from injury to enrollment, and baseline CRS score). Two‐sided p values ≤ 0.05 will be considered significant. The pairwise deletion method is used to handle missing data. Statistical analysis will be performed with SPSS version 22 software (SPSS Inc., Chicago, IL, USA).

EEG data are analyzed using MATLAB 2016b (Mathworks, Sherborn, Massachusetts, USA). The immediate effects of EA are explored by analyzing the mean EEG power, pattern, and connectivity at 10 min before the allocated treatment and at four time points after the allocated treatment (10 min, 60 min, 6 h, and 24 h). The prolonged effects of EA are explored by analyzing changes in EEG power, pattern, and connectivity before and after the 14‐day intervention. For each electrode, the mean power values of 5 s epochs are estimated in different standard EEG frequency bands: delta (0.5–4 Hz), theta (4–8 Hz), alpha (8–13 Hz), and beta (13–30 Hz). EEG patterns are determined based on the EEG power spectrum and classified into four categories according to the “ABCD” model, which decodes the integrity of thalamocortical circuitry and the preservation of consciousness (Alkhachroum et al. 2020; Edlow et al. 2021). Functional connectivity is estimated using phase‐synchronization measures. Sleep EEG is rated using the modified Valente's Grade (Yang et al. 2020). For SEP data, the average of N20–P25 peak‐peak amplitude from the right and left sides is calculated. For BAEP, wave IV–V peak‐to‐peak amplitude, wave V latency in ms, and interpeak latency difference (IPL) III–V are selected as main variables.

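### The adjusted model for BCI accuracy leaves out baseline BCI accuracy, which the trial plans to measure in all patients, and so gives up precision on this secondary outcome

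*Protocol article*

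**What the plan says.** Section 2.13 defines the primary outcome as a change from baseline: "The primary outcome of the change in CRS‐R score after 14‐day treatment". BCI accuracy is named differently, as the value reached: "secondary outcomes of BCI accuracy after 14‐day treatment". Each outcome gets an unadjusted two-sample test (t or Mann-Whitney) and a bootstrapped general linear model. A single covariate list serves CRS-R, BCI accuracy and GOS-E: "adjusted for age, sex, time from injury to enrollment, and baseline CRS score".

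The baseline BCI value is planned. The Abstract says all patients have CRS-R and BCI assessments before and after the 14 days. Section 2.8 states that the listed "examinations are performed before the first EA or sham‐EA treatment", and that list ends with "neurite orientation dispersion and density imaging (NODDI), and BCI". Table 1 marks BCI at both the pre-treatment and the post-treatment visit.

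**The concern.** CRS-R enters as a change and is also adjusted for its own baseline. BCI accuracy, measured at the same two stages, gets neither. As specified, the baseline BCI assessment is used in neither between-group comparison of BCI, and the article gives no reason for the difference.

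Baseline CRS-R can stand in only in part. The Discussion brings in BCI as a complement to the CRS-R because some patients may have awareness that behavioural scales miss. The randomization strata (UWS, MCS) are themselves CRS-R diagnoses, so they do not secure balance on BCI ability.

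With 25 patients per arm, the difference between arms in mean baseline BCI has a standard error of sqrt(2/25) = 0.28 SD. About one trial in three would by chance show an imbalance larger than that. What is at stake is the width of the confidence interval for one secondary outcome, and how easily a chance baseline difference could be mistaken for a treatment effect or hide one.

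**Working it through.** **The plan's own figure.** Section 2.12 gives a difference of 1.3, SD 1.6, two-sided 5% and 24 per group. Power is not stated; 80% is assumed here. n = 2 × (1.6 × (1.960 + 0.842) / 1.3)² = 23.8, so 24; and 24 / 0.96 = 25 per group. The figure reproduces, but it concerns CRS-R. The article gives no SD, effect or power for BCI accuracy.

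**Effect of adding the baseline.** Let r be the partial correlation of baseline with post-treatment BCI accuracy, given the four listed covariates. Adding the baseline multiplies the variance of the treatment effect by 1 − r². With 48 patients analysed (2 × 24), residual degrees of freedom fall from 48 − 6 = 42 to 41. The penalty for the extra covariate is taken as (42 − 2)/(41 − 2) = 40/39. So

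SE ratio = sqrt((1 − r²) × 40/39); equivalent extra patients, without penalty = 1/(1 − r²) − 1.

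| r (assumed) | 1 − r² | SE ratio, no penalty | SE ratio, with penalty | Equivalent extra patients |
|---|---|---|---|---|
| 0 | 1.00 | 1.000 | 1.013 | 0% |
| 0.2 | 0.96 | 0.980 | 0.992 | 4% |
| 0.3 | 0.91 | 0.954 | 0.966 | 10% |
| 0.5 | 0.75 | 0.866 | 0.877 | 33% |
| 0.6 | 0.64 | 0.800 | 0.810 | 56% |
| 0.7 | 0.51 | 0.714 | 0.723 | 96% |

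Break-even is at (1 − r²) × 40/39 = 1, so r² = 1/40 and r is about 0.16.

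**Allowing for baseline CRS-R, already in the model.** Assume a raw baseline-to-post BCI correlation of 0.6, and a correlation c of baseline CRS-R with BCI accuracy that is the same at both times. Age, sex and time from injury are ignored. Then r = (0.6 − c²)/(1 − c²).

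| c (assumed) | r | SE ratio, no penalty | Equivalent extra patients |
|---|---|---|---|
| 0.3 | 0.51/0.91 = 0.56 | 0.83 | 46% |
| 0.5 | 0.35/0.75 = 0.47 | 0.88 | 28% |
| 0.7 | 0.11/0.51 = 0.22 | 0.98 | 5% |

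The gain is therefore worthwhile unless baseline CRS-R already carries most of the information in baseline BCI.

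**The case against.** The best counter-argument is that the gain may be small. Only the partial correlation counts, and the article gives none. If the raw BCI correlation were 0.5 and the CRS-BCI correlation 0.7, r would be (0.50 − 0.49)/0.51 = 0.02 and nothing would be gained. BCI accuracy is also noisy: with 50 trials at 50% accuracy the binomial SD is sqrt(0.25/50) = 0.07, which weakens r. This stands as a limit on the size of the gain. It is no reason to leave the baseline out, since the worst case costs about 1% in standard error.

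A second objection also stands. Section 2.13 handles missing data by deletion, so a patient without a usable baseline BCI could be lost from the enlarged model. The fix has to deal with this.

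It might also be said that BCI was meant as a change score, or that one list for three outcomes is an article's shorthand. As printed, the word for change attaches only to CRS-R and the list applies to BCI. Even for a change score, baseline adjustment would help: with equal variances and raw correlation ρ, 1 − ρ² never exceeds 2(1 − ρ).

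A reader might infer that patients who could already do the BCI task would be counted as treatment successes. The article does not support that. It has no patient-level success rule; accuracy is a proportion of trials, and 1:1 randomization spreads able patients evenly in expectation. Nor should the point be extended to all repeated measures. The covariate list covers only CRS-R, BCI and GOS-E, and Section 2.13 already analyses prolonged EEG effects and fMRI low-frequency amplitude as changes.

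**Conclusion.** The point holds as a loss of precision on one secondary outcome. It is not a bias, it does not inflate the type I error, and it leaves the primary analysis untouched. Chance imbalance in baseline BCI stays uncorrected beyond what age, sex, time from injury and baseline CRS-R explain.

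The likely size runs from a standard error about 1% larger (r near 0) to about 28% smaller (r = 0.7). In the illustration that allows for CRS-R, the gain equals 5% to 46% more patients. It would be tempting to quote 33% to 96% outright, but those figures hold only if the partial correlation itself reaches 0.5 to 0.7. All correlations are assumptions; what rests on the text alone is that the list omits a baseline the trial plans to collect.

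**What to change.** Before unblinding, add baseline BCI accuracy as a covariate in the BCI model only, keeping the four covariates already listed. Report the adjusted mean difference in percentage points with its 95% CI, in place of the odds ratio that Section 2.13 names as the output of its adjusted models. Keep patients with a missing baseline BCI by a simple baseline imputation, such as the overall mean across both arms, so that the deletion rule does not remove them.

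The cost is one degree of freedom and one sentence on missing baseline values. No new data, visits or patients are needed.

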### Assessment of the Level of Consciousness

2.9

The level of consciousness is assessed using CRS‐R scores and a BCI system (Figure 3), which is conducted by trained researchers who are blinded to the grouping results. The CRS‐R has a maximum score of 23 points (higher scores indicate higher levels of consciousness) and consists of 23 items broken into 6 subscales: auditory, visual, motor, verbal, communication, and arousal functions. The Chinese version of CRS‐R is used in this study (Di et al. 2017; Zhang et al. 2019). All patients receive three CRS‐R assessments administered at 24‐h intervals​​ during both pre‐treatment screening and post‐treatment evaluation. Diagnoses of UWS, MCS (including MCS‐ and MCS+), and emergence from the minimally conscious state (EMCS) are based on at least two CRS‐R assessments (Bruno et al. 2011; Giacino et al. 2002), with the higher score designated as the baseline and outcome CRS‐R score for each patient. Additionally, daily CRS‐R assessments are conducted throughout the 14‐day treatment period.

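### The plan says all randomised patients are analysed, but pairwise deletion drops anyone without a post-treatment CRS-R from the primary comparison and leaves their daily scores unused

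*Protocol article*

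**What the plan says.** Section 2.13 (Statistical and Analytical Plan) invokes intention to treat and says that "all patients who are randomized are included in the analysis of the original allocation group". The same paragraph then gives the only missing-data rule in the article: "The pairwise deletion method is used to handle missing data". The variable affected first is "The primary outcome of the change in CRS‐R score after 14‐day treatment", compared between arms by a t-test or a Mann-Whitney test. A general linear model follows, adjusted for age, sex, time from injury and baseline CRS score.

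CRS-R is also measured throughout treatment. Section 2.8 (Study Procedures) states: "During the 14 days of treatment, the CRS‐R score is assessed every day after the treatment". Section 2.9 (Assessment of the Level of Consciousness) confirms that "daily CRS‐R assessments are conducted throughout the 14‐day treatment period". That section also provides for three assessments, 24 hours apart, both at screening and after treatment, "with the higher score designated as the baseline and outcome CRS‐R score for each patient". The analyses described in Section 2.13 do not use the daily scores.

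**The concern.** For a single change score per patient, pairwise deletion is an available-case analysis. Whoever lacks the post-treatment score is removed, so the promise to include everyone fails as soon as one primary outcome is missing.

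Deletion is safe only if loss is unrelated to outcome, given what the analysis conditions on. The unadjusted test conditions on arm alone. The article gives no loss rate and no list of causes, but outcome-related loss is plausible from its own content:
- Patients enter 7 to 90 days after TBI, in UWS or MCS (Section 2.4).
- Serious adverse events may lead to suspension or termination of the allocated intervention (Section 2.14).
- The outcome needs assessments that continue after the last session (Section 2.9).

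At stake are the size of the estimated effect and the power of a trial of 25 per arm. The scores observed before a patient is lost carry information on the missing value, and the stated analysis discards it.

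**Working it through.** **1. The plan's own figure.** Inputs from Section 2.12: difference 1.3, SD 1.6 (given for the sham arm, used here for both), two-sided 5% error. Power is not stated; 80% is assumed.

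- n per arm = 2 × (1.96 + 0.842)² × 1.6² / 1.3² = 23.8, rounded up to 24. This matches the stated minimum (90% power would give 32).
- 24 / (1 − 0.04) = 25 per arm, 50 in total, as stated.
- 4% of 25 = 1 patient. A second loss leaves 23, below the stated minimum of 24.

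**2. Power after deletion**, with the same inputs and equal loss in both arms:

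| Missing per arm | Analysed per arm | Power (normal) | Power (t) |
|---|---|---|---|
| 0% | 25 | 81.9% | 80.4% |
| 4% | 24 | 80.4% | 78.7% |
| 10% | 22.5 | 77.8% | 75.9% |
| 20% | 20 | 72.9% | 70.7% |

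**3. Bias from loss in one arm only.** Let k of 25 patients be lost, with unobserved changes on average d points below the mean of those who remain. The full-arm mean is [(25 − k) × m + k × (m − d)] / 25 = m − k × d / 25, where m is the observed mean. Deletion therefore overstates that arm's mean by k × d / 25. The values of k and d are assumptions.

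- k = 3, d = 2: 3 × 2 / 25 = 0.24, and 0.24 / 1.3 = 18% of the target.
- k = 3, d = 4: 3 × 4 / 25 = 0.48, and 0.48 / 1.3 = 37%.
- k = 5, d = 2 to 4: 0.40 to 0.80.

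With no selective loss in the other arm, this is also the bias in the difference. It inflates the EA effect if the loss is in the EA arm and shrinks it if the loss is in the sham arm.

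**4. Simulation of both patterns.** Assumptions: 25 per arm, true difference 1.3, SD 1.6, correlation 0.7 between a mid-treatment score and the final score, 4,000 replicates.

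| Missing per arm | Low scorers lost in EA, random loss in sham: deletion | Same pattern, mid-treatment score used | Low scorers lost in both arms: deletion |
|---|---|---|---|
| 4% | 1.41 | 1.31 | 1.31 |
| 10% | 1.51 | 1.30 | 1.30 |
| 20% | 1.70 | 1.30 | 1.30 |

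Bias in the difference arises when selective loss is unequal between arms. In this setting, using an observed intermediate score within each arm removes it. The simulation makes loss depend on that observed score, which is the case most favourable to the repair.

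**The case against.** Five points can fairly be made on the other side.

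- **The contradiction is partial.** Deletion does not move anyone out of the allocated arm, so that half of the intention-to-treat statement stands. Only the inclusion of all randomised patients fails. Relabelling would cure the wording, though not any bias.
- **The bias is conditional.** A reader might take 0.24 to 0.48 points as the expected bias in the treatment effect. The documents do not support that. It is the error in one arm's mean, and it carries over to the difference only if the other arm has no comparable selective loss. The loss of 3 in 25 and the 2 to 4 point deficits (1.25 to 2.5 times the assumed SD) are assumptions. Section 2.4 also excludes unstable and sedated patients at entry. All of this stands.
- **The daily data are less complete than they look.** A reader might infer that 14 daily scores exist for every lost patient. Someone who leaves early has fewer. A daily score also appears to be a single assessment, whereas the outcome is the higher of repeated ones, so daily scores can inform the outcome but not replace it. A patient who misses only some of the post-treatment assessments may still have an outcome.
- **The adjusted and unadjusted analyses use the same patients.** A reader might suspect that deletion gives them different patient sets. The adjustment covariates are recorded at screening (Section 2.8 and Table 1), so anyone with a primary outcome should have them all.
- **Detail belongs in the analysis plan.** Silence in a condensed article on sensitivity analyses, or on a separate analysis of the daily scores, is no fault. The deletion rule is different, because the article states it.

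**Conclusion.** The point holds in a limited form. Section 2.13 promises an all-randomised analysis and fixes a rule that cannot deliver it once a post-treatment CRS-R is missing. That rule also sets aside relevant data already collected.

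The size depends on a loss mechanism that the documents do not give. Under one-arm loss of 3 in 25 with a 2 to 4 point deficit, the difference shifts by 0.24 to 0.48 points, 18 to 37% of the 1.3-point target. Under similar selective loss in both arms there is little bias. Power still falls, to about 76 to 78% at 10% missing, given an assumed 80% design power and a common SD of 1.6. The margin over the stated minimum is one patient per arm. This should be corrected before unblinding, but it does not undermine the design.

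**What to change.** For the primary outcome, replace pairwise deletion in Section 2.13 with one prespecified method:

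- a mixed model on the baseline, daily and post-treatment CRS-R, with the post-treatment score given its own mean because it is the higher of repeated assessments; or
- multiple imputation of the post-treatment score from baseline score, UWS/MCS stratum, arm and a small summary of the daily scores, such as the last one observed.

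Either model must be kept small. Baseline, 14 daily and one post-treatment occasion make 16, and an unstructured covariance would need 16 × 17 / 2 = 136 parameters from 50 patients.

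Do not impute CRS-R after death under missing-at-random. Give deaths their own prespecified analysis rule, for example a worst-rank analysis. Keep the available-case analysis as a sensitivity analysis. If pairwise deletion is retained as the main method, describe the analysis as available-case and withdraw the all-randomised claim.

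The cost is a revised paragraph, a stated missing-at-random assumption that the data cannot verify, and modest extra analysis work. No new patients, visits or measurements are needed.

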### Trial Interventions

2.7

All patients receive routine standardized neurocritical care management, including airway management, temperature regulation, blood pressure control, electrolyte balance maintenance, infection control, nutritional support, etc. Additionally, all patients undergo passive range of motion therapy and ergometer cycling therapy daily, administered by a physiatrist blinded to the group allocation.

All patients receive EA or sham‐EA treatment in the supine position at 9 am for 30 min once a day for 14 consecutive days (Figure 2). One certified acupuncturist performs EA and sham‐EA treatments for patients in both groups. Disposable sterile acupuncture needles (0.25×25 mm, Hanyi brand, Changchun AIK Medical Devices Co., China) and EA apparatuses (SDZ‐V, Hwato Brand, Suzhou Medical Appliance Factory, China) are used in both groups.

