### Neurophysiological Assessments

2.10

All patients receive two times of video‐EEG monitoring. The first EEG recording starts 20 min before the first EA or sham‐EA treatment and continues until 24 h after the treatment. The second EEG recording starts 20 min before the last EA or sham‐EA treatment and continues until 24 h after the treatment. EEG signals are collected through 19‐channel monopolar leads with Ag/AgCl cup electrodes (NicoletOne EEG System, USA), placed according to the international 10–20 system. The sampling frequency is 500 Hz and the electrode–skin impedance is lower than 5 kΩ.

All patients receive SEP and BAEP assessments before and after the 14‐day EA or sham‐EA treatment (Nicolet Monitor UltraPro S100, US). All SEPs and BAEPs are assessed for reproducibility and analyzed by one certified neurophysiologist. For SEP, monophasic rectangular‐wave 200 µs stimulus pulses are given to the median nerve, and the intensity is adjusted to produce a visible thumb twitch. A minimum of 500 stimulations are averaged per recording. For BAEP, monoaural click stimuli of 50 µs duration are delivered through shielded headphones at a frequency of 10 Hz and an intensity of 70–90 dB HL. Both ears are stimulated separately. The contralateral ear is masked by 20 dB noise. Three trials of 1,000 clicks are recorded to assess reproducibility.

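### With daily 9 am sessions, the 24 h EEG point of the first recording coincides with session 2, so it cannot show the lasting effect of session 1

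*Protocol article*

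**What the plan says.** Three sections of the protocol article together fix the timing.

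- **Trial Interventions (2.7):** all patients are treated "in the supine position at 9 am for 30 min once a day for 14 consecutive days". The stimulator is set to 4 Hz/20 Hz. The cords used in the sham arm do not conduct.
- **Neurophysiological Assessments (2.10):** "The first EEG recording starts 20 min before the first EA" or sham session and "continues until 24 h after the treatment". The second recording is built the same way around the last session.
- **Statistical and Analytical Plan (2.13):** immediate effects compare a point 10 min before treatment with EEG "at four time points after the allocated treatment (10 min, 60 min, 6 h, and 24 h". The measures are power, pattern (the ABCD class) and connectivity. Prolonged effects compare the same three measures before and after the 14-day course.

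Sleep appears as a key EEG parameter in Table 2 and in one sentence of 2.13: "Sleep EEG is rated using the modified" Valente grade. Study Procedures (2.8) lists EEG among the examinations done before the first treatment.

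The article does not say whether the 24 h are counted from the start or the end of a session. It neither exempts day 2 from the 9 am session nor places the 24 h epoch before it.

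**The concern.** The 24 h point is the only one of the four that can show whether the effect of a single session lasts until the next day. With a daily schedule at a fixed hour, 24 h after one session is also the time of the next. EEG taken then reflects both sessions, and no analysis can separate them.

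Randomisation does not remove the problem, because only the EA arm receives current. An acute response to session 2, or any pick-up of the stimulating current, would appear as a difference between arms and be read as a late effect of session 1. The stimulation frequencies fall within the analysed spectrum: 4 Hz is the boundary between delta and theta, and 20 Hz lies in beta. The ABCD class is derived from the power spectrum, so it would be exposed as well.

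The same label would also mean different things in the two recordings, since no session follows the last one.

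**Working it through.** The plan gives no figure of its own here, so the check is clock arithmetic on its schedule.

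**Inputs**
- Session k runs 09:00–09:30 on day k, for k = 1 to 14 (2.7). Session 2 is therefore day 2, 09:00–09:30, and there is no session on day 15.
- Each recording starts 20 min before its session and ends 24 h after it (2.10).
- Immediate-effect points: 10 min before; 10 min, 60 min, 6 h and 24 h after (2.13).

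**Step 1. Place the points of the first recording.** Clock time = zero time + lag, with the zero time taken both ways because the article does not fix it.

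| Lag | Zero = end of session 1 (09:30) | Zero = start of session 1 (09:00) |
|---|---|---|
| 10 min | 09:40 | 09:10, inside session 1 |
| 60 min | 10:30 | 10:00 |
| 6 h | 15:30 | 15:00 |
| 24 h | day 2, 09:30: end of session 2 | day 2, 09:00: onset of session 2 |
| Recording length from 08:40 | 24 h 50 min | 24 h 20 min |

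**Step 2. Choose the coherent reading.** Counting from the start puts the 10 min point in the middle of stimulation, which is not after treatment. Counting from the end keeps the first three points clear of any session, and it is the only reading under which the 10 min point makes sense. Under it the 24 h point is the end of session 2. If the recording also stops there, as 2.10 says, signal taken just before that point lies inside session 2.

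**Step 3. Compare with the last recording.** Session 14 ends on day 14 at 09:30, so its 24 h point is day 15 at 09:30. No session takes place that day. The two 24 h points are not alike.

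**Step 4. Size.** One of 4 post-treatment points is affected in one of 2 recordings. If both recordings are used, that is 1 of 2 × 4 = 8 post-treatment readings.

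**Step 5. Is a clean substitute already recorded?** The pre-treatment point is 09:00 − 10 min = 08:50. At 08:50 on day 2, session 2 has not begun, and the recording is still running under either reading (it ends at 09:00 or 09:30). Time since the end of session 1 is 24 h − 40 min = 23 h 20 min. The same clock time on day 15 lies inside the last recording.

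**Step 6. Sleep.** The first recording has 20 min before session 1 (08:40–09:00). Its only night is that of day 1 to day 2, after session 1.

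**The case against.** **A start-based count could give a clean epoch.** If the recording stops at 09:00 on day 2, its last epoch precedes session 2. Table 2 gives the EEG duration as 24 h, slightly nearer to 24 h 20 min than to 24 h 50 min. This is a fair point, but the same count puts the 10 min point inside session 1. One of the two points fails either way, unless the zero time is stated and the epoch placed explicitly.

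**The article does not say which recording serves the immediate-effect analysis.** If only the last one did, there would be no collision. Nothing in 2.13 restricts it so, and 2.10 gives both recordings the same 24 h tail.

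**Artefact is not shown.** A reader might infer that the 24 h EEG is contaminated by 4 Hz/20 Hz current. The documents do not support that: the window averaged around each point is not given, so whether stimulated signal enters it is unknown. The mixing of two sessions' effects does not depend on artefact.

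**A stronger reading on baseline and sleep fails.** A reader might infer that the EEG has no pre-treatment value, or that a planned before/after sleep comparison is invalid. Power, ABCD class and connectivity do have a genuine 20 min pre-treatment segment, and it covers the point 10 min before. For sleep, 2.13 states no before/after contrast and calls no night a baseline. Such a contrast can only be inferred from EEG being described as a before-and-after examination with sleep as a key parameter. Only a conditional caution is justified.

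**EEG is exploratory.** This stands, and it limits the weight of the point.

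**Conclusion.** The point holds, with limited reach. Followed as written, the 24 h reading of the first recording falls at the end of session 2, or at its onset on the less coherent count. It cannot be interpreted as the next-day effect of session 1, and it does not match the 24 h reading of the last recording.

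This rests on three assumptions: sessions keep to 9 am on consecutive days as stated; the 24 h are counted from one end of the session or the other; and the first recording is used for immediate effects.

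The other three post-treatment points of the first recording, all points of the last recording, the prolonged-effect contrast on power, pattern and connectivity, the secondary outcomes (BCI accuracy and GOS-E) and the primary CRS-R outcome are unaffected. No sample size or error rate depends on it. It is nonetheless worth settling before the EEG data are examined, because choosing the epoch afterwards would be post hoc.

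On sleep, the conclusion is conditional: if a before/after comparison is made, the first night is not a pre-treatment value.

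**What to change.** Leave the treatment timing alone and change the measurement definition.

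1. In 2.10 and 2.13, state the zero time from which 24 h is counted.
2. Define the last point of the first recording as the final epoch before the day-2 session starts, at about the same clock time as the pre-treatment epoch (for example 08:50), and label it as such.
3. Use the same clock time in the last recording, so that the two late points are comparable with each other and with their pre-treatment points.
4. If sleep grade is analysed, do not call the first night a pre-treatment baseline. Compare the arms on the sleep grade of the last recording. No additional overnight recording is needed.

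**Cost:** a few sentences of wording. The signal is already being collected, and neither treatment nor electrode time changes. The late point becomes slightly less than 24 h after treatment (23 h 20 min from session end if 08:50 is used), which its label should say. For sleep, the price is giving up a within-patient change, which the first night could not have provided cleanly.
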